### Process evaluation

Process evaluations are highly valuable for understanding how discrepancies between the expected and observed outcomes may be related to context influences and implementation issues arising in complex interventions [6]. In the present study, the process evaluation of both implementation issues and context is based on the approach suggested by Linnan and Steckler [25], in which special consideration is put to the degree of receptivity and engagement of the workers to the intervention. Moreover, since previous research has shown that employees are more likely to participate in the activities of interventions, if they believe they can influence the intervention contents [26], group-related processes associated with the so-called collective self-efficacy [27] will also be taken into account. It is hypothesised that workers will be more engaged in the intervention, if they believe the group is capable of achieving the intervention goals (i.e., high collective self-efficacy). The evaluation will be based on information collected in questionnaires which were developed specifically for this intervention on the basis of previous literature reviews on process evaluation [28–30]. The questionnaires collect information on the assessment of the study participants on several process variables which have been identified in the pertinent literature as decisive for the attainment of intervention goals such as perceived support by management, conflict and collaboration in workshop groups, the expected personal benefit from the intervention, and the feasibility of intervention activities. Furthermore, according to those literature reviews, support from key stakeholders such as managers and supervisors may have a substantial impact on the intervention outcomes. Since most members of the initiatives circles described above have a leading position, specific questionnaires will be developed and deployed among the members of those circles. The adequacy of the newly developed questionnaires will be investigated in a pretest phase including cognitive Interviews and psychometric analyses.

## Results

The flow diagram of the number of individual participants and clusters from recruitment to baseline is provided in Fig. 2. Total response rates for workers and patients at baseline were about 13 and 53%, respectively. The socio-demographic characteristics of workers and clients, and the descriptive statistics of the main outcomes in both the intervention and control groups are reported in Tables 1 and 2. In the 11 health organisations participating in the intervention, total of 67 clusters were defined covering about 68% of all wards and including 24 health services areas such as anaesthesia, intensive care units, geriatrics, psychiatry, surgery, cardiology, paediatrics, urology, trauma surgery and emergency. Since most participating organisations are general hospitals providing a similar range of health services, the specific characteristics of clusters across organisations are rather balanced: It was found that for 57 clusters there were at least two clusters of a similar health service type in two different hospitals. For instance, for two intensive care clusters in two different hospitals, one intensive care cluster in one hospital was assigned to the intervention group, and the other cluster to the control group.

**Table 1 Tab1:** Descriptive statistics of the healthcare workers datasets. Percent values for categorical variables, means and standard deviation in parentheses for continuous variables. Missing values per variable or scale

Variable	Control	Intervention	Missing
**Healthcare workers (*****n*** **= 386)**			
*Age*			1
Age 18–39	23.1	27.2	
Age 40–54	52.5	46.3	
Age 55 and older	24.4	26.5	
*Sex*			5
Male	23.0	16.4	
Female	77.0	83.6	
*Psychometric scales*			
Physical work ability	3.15 (0.98)	3.10 (0.91)	4
Mental work ability	3.05 (0.94)	3.04 (0.87)	6
Cognitive demands	4.29 (0.46)	4.32 (0.41)	1
Emotional demands	3.81 (0.62)	3.85 (0.57)	2
Low job control	3.24 (0.65)	3.14 (0.67)	1
Low predictability of work tasks	2.87 (0.70)	2.83 (0.73)	1
Role clarity	2.16 (0.62)	2.11 (0.70)	2
Role conflict	3.12 (0.75)	3.19 (0.77)	1
Low development chances	2.30 (0.62)	2.20 (0.63)	1
Efforts	2.62 (0.69)	2.58 (0.61)	4
Rewards	1.84 (0.59)	1.82 (0.53)	23
Effort-Reward Imbalance	0.89 (0.40)	0.85 (0.32)	26
Overcommitment	2.59 (0.61)	2.59 (0.56)	2
Supervisor behaviours	3.16 (0.94)	3.16 (0.95)	3
Unsupportive colleagues	1.88 (0.67)	1.94 (0.74)	2
Negative affect	1.86 (0.64)	1.77 (0.55)	3

**Table 2 Tab2:** Descriptive statistics of the clients datasets. Percent values for categorical variables, means and standard deviation in parentheses for continuous variables. Missing values per variable or scale

Variable	Control	Intervention	Missing
**Patients (*****n*** **= 632)**			
*Age*			4
Age 18–49	22.9	17.5	
Age 50–69	38.4	27.9	
Age 70 and older	38.7	54.6	
*Sex*			2
Male	47.1	50.0	
Female	52.9	50.0	
Length of hospital stay (days)	7.26 (7.84)	6.90 (7.61)	5
*Psychometric scales*			
Trust	3.71 (0.46)	3.77 (0.38)	4
Support	3.58 (0.57)	3.68 (0.46)	28
Availability	3.57 (0.51)	3.64 (0.44)	2
Decisional control	4.36 (0.56)	4.35 (0.51)	4
**Individuals in elderly care (*****n*** **= 150)**			
*Age*			0
Age 50–79	42.9	24.2	
Age 80–89	50.0	49.5	
Age 90 and older	7.1	26.3	
*Sex*			0
Male	42.9	28.4	
Female	57.1	71.6	
Years being in elderly care	4.54 (3.74)	3.96 (3.78)	8
*Psychometric scales*			
Trust	3.29 (0.72)	3.76 (0.43)	7
Support	3.07 (0.82)	3.60 (0.45)	9
Decisional control	4.10 (0.89)	4.47 (0.67)	12
Person-focused care	3.19 (1.04)	3.30 (1.20)	10

The estimates of the effective sample size (N_eff_) and the ICC corresponding to the workers’ physical and mental work ability were N_eff_ = 345 and 423, and ICC = 0.05 and 0.01, respectively. The average cluster size in the workers sample was m = 6.53, which yields design effect estimates of DE = 1.29 and 1.05 for the main outcomes. Thus, it will be possible to estimate effect sizes of at least 0.30 and 0.27 at the 80% power and 5% significance levels, for the workers’ physical and mental work ability, respectively. The estimates for the patients dataset were N_eff_ = 234, average ICC = 0.09, m = 19.5, and DE = 2.7. Since data of approximately 1200 additional patients will be collected cross-sectionally at the T1 and T2 follow-ups, a final effective sample size of approximately 234*3 = 702, and an average effect size of about 0.21 concerning patients satisfaction with care may be estimated at the 80% power and 5% significance levels. Finally, the power analysis for the elderly care dataset yielded an average ICC = 0.17, m = 30.7, and DE = 6.32, and an effective sample size of 24 per survey. Thus, for this dataset, at the end of the study, an effect size of about 0.66 can be estimated at the 80% power and 5% significance levels with a final effective sample size N_eff_ = 74 of elderly care clients.

The results of the statistical analyses at baseline are reported in Tables 3 and 4 for workers and clients, respectively. There were no baseline differences between the intervention and control groups in the datasets regarding the main outcomes of the study. Among workers, it was found that higher scores of effort-reward imbalance and overcommitment are associated with lower scores of physical and mental work ability (Table 3). These associations seem to be partly mediated by the levels of negative affect, and physical and mental health perceptions, as indicated by the lower magnitude of the regression coefficients in the fully adjusted models (models 2 and 3 in Table 3, respectively). Among patients, the results did not suggest any association between the perceived effort-reward imbalance and overcommitment of healthcare workers at the cluster level and patients’ satisfaction with care (Table 4).

**Table 3 Tab3:** Bayesian linear mixed models for the healthcare workers dataset (complete cases). Dependent variables: physical and mental work ability. Model 1 is adjusted for age, gender, and intensive care unit vs. other wards. Model 2 adjusts also for negative affect and organisation type (general hospital vs. getriatric and psychiatric hospitals). Model 3 is the fully adjusted model with physical and mental health component scores. Beta: regression coefficient, SE: standard error, and 95% CI: confidence intervals at the 95% level. ERI: effort-reward imbalance. DIC: deviance information criterion. *N* = 346

Variable	Physical work ability						Mental work ability					
	Model 1		Model 2		Model 3		Model 1		Model 2		Model 3	
	Beta (SE)	95% CI	Beta (SE)	95% CI	Beta (SE)	95% CI	Beta (SE)	95% CI	Beta (SE)	95% CI	Beta (SE)	95% CI
Intercept	4.79 (0.28)	[4.20; 5.29]	5.00 (0.30)	[4.40; 5.59]	−0.18 (0.72)	[−1.61; 1.12]	4.90 (0.27)	[4.38; 5.42]	5.51 (0.28)	[4.90; 6.00]	2.35 (0.68)	[1.07; 3.78]
Intervention (ref. control)	− 0.10 (0.11)	[− 0.32; 0.10]	− 0.09 (0.11)	[− 0.32; 0.12]	− 0.06 (0.11)	[− 0.28; 0.14]	− 0.05 (0.11)	[− 0.26; 0.16]	− 0.09 (0.11)	[− 0.31; 0.10]	− 0.04 (0.11)	[− 0.27; 0.15]
ERI	− 0.80 (0.17)	[−1.13; − 0.50]	− 0.59 (0.18)	[− 0.92; − 0.24]	− 0.24 (0.18)	[− 0.58; 0.09]	− 0.42 (0.17)	[− 0.74; − 0.10]	−0.12 (0.19)	[− 0.50; 0.24]	0.01 (0.18)	[− 0.33; 0.37]
Overcommitment	−0.28 (0.11)	[− 0.50; − 0.09]	− 0.15 (0.12)	[− 0.38; 0.07]	− 0.04 (0.11)	[− 0.26; 0.18]	−0.56 (0.11)	[− 0.76; − 0.35]	−0.38 (0.11)	[− 0.62; − 0.19]	−0.25 (0.11)	[− 0.47; − 0.05]
DIC	881		874		773		863		827		793	
Residual variance	0.884		0.874		0.783		0.866		0.831		0.800

**Table 4 Tab4:** Bayesian linear mixed models for the clients datasets (complete cases). The models for the patients dataset are adjusted for age, gender, organisation type (general hospital vs. getriatric and psychiatric hospitals), general health, and education. The models for the elderly care dataset are adjusted for age, gender, general health, and education. Beta: regression coefficient, SE: standard error, and 95% CI: confidence intervals at the 95% level. DIC: deviance information criterion. Effort-reward imbalance (ERI) and overcommitment values correspond to the average of psychosocial load of workers at the cluster level

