**Results:**

There was no evidence of substantial differences between trial arms at baseline concerning the outcomes. The design effect estimates for physical and mental work ability were 1.29 and 1.05, respectively. At the end of the trial, effect sizes of at least 0.30 and 0.27 at the 80% power and 5% significance levels can be attained.

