### Sample size

The sample size was calculated with the formulae provided by Dreyhaupt et al. (2017) [15], which considers the intraclass correlation coefficient (ICC), the average cluster size (m), the number of clusters (J), and the design effect (DE). The approach for calculating the sample size was to estimate the minimum effect attainable for a given sample and cluster size. An estimate of the ICC = 0.037 was taken from the intervention study of Mongini et al. (2012) conducted with a sample of Italian public servants [16]. Furthermore, it was assumed that a total of 50 clusters could be expected with an average cluster size of m = 5. Under these assumptions, a design effect DE = 1 + ICC*(m-1) = 1.33 was estimated, so that a total sample size of 500 participants was found to be required in order to detect a minimum effect of 0.30 at the 80% power and 5% significance levels. A total sample size of 500 individuals in a cluster-randomised design corresponds to an effective total sample size of 375 in a study with individual randomisation [15].

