### Randomisation and implementation

Healthcare workers registered for the surveys by filling out a registration form addressed to Ulm University including personal information and the name of the ward they usually work in. Wards were then aggregated by the authors at Ulm University in clusters as described above, and stratified by hospital and elderly care ward. A list containing hospitals, clusters and number of registered participants was provided by the first author to the Institute of Epidemiology and Medical Biometry at Ulm University which generated the random allocation sequence and assigned clusters to interventions for the hospitals, independently from the authors at Ulm University and the consultants providing the intervention. The randomisation of clusters in the hospitals was performed in two steps with the statistical environment R. In the first step, the probability of being assigned to the intervention group was proportional to cluster size in each hospital, and a total of 10 clusters (i.e., one intervention cluster per hospital) were allocated to the intervention arm. Given the large variation of cluster sizes (Fig. 2), a sampling schedule proportional to size was required in the first step in order to ensure the generalisability of results by including the largest clusters in the hospitals, and to counter the expected power loss due to cluster and individual sample attrition in the subsequent follow-up measurements. In the second step, the random allocation proceeded by simple random sampling. However, given that only four consultants provide the intervention, a 1:1 allocation scheme for the remaining clusters was not feasible due to personnel limitations. Thus, the number of additional clusters in the intervention group in the hospitals was limited to 10. On the other hand, since the elderly care centre comprises only four wards, a simple random allocation in proportion 1:1 was performed in that case by the first author at Ulm University.

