## Discussion

The results at baseline suggest that the random allocation of clusters was satisfactory, since no substantial differences were observed between the intervention and control arm regarding the primary outcomes. According to the power analyses reported in the results section, one strength of the intervention is that effect sizes of at least 0.30 and 0.27 can be estimated at the 80% power and 5% significance levels, for physical and mental work ability of workers, respectively. Given that previous randomised organisational interventions have reported even larger effect sizes (standardised mean differences of − 1.23, − 0.55 and − 0.35) [7], the present study has sufficient power to detect substantial changes in the main outcomes.

A further strength of the study concerns the indication of an acceptable internal validity. Mainly successfully and widely tested questionnaires showing satisfying to good psychometric properties in previous studies [24, 31–35] and the present intervention as well (average Cronbach’s alpha over all instruments 0.74, see Supplementary material 1), were applied to measure independent (e.g., workload) and dependent variables (e.g., work ability, clients’ satisfaction). These measures allow comparisons of the present results with findings from other studies. Concerning the first study hypothesis, the results show associations of measures of effort-reward imbalance with work ability in workers. Hence, it is plausible to expect that a reduction of workload may result in increases of perceived work ability. In addition, the results indicate that these associations are mediated by perceived health (model 3 in Table 3). This mediation has been hypothesised previously, but has not been shown empirically so far [36]. However, the second hypothesis stating that the reduction of workload increases patients satisfaction did not receive support, since no cross-sectional associations were observed between workload and patients satisfaction (Table 4). Due to the low number of clusters in the elderly care centre, the second hypothesis cannot be investigated with the elderly care dataset.

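### The detectable effects of 0.30 and 0.27 for the primary outcome rest on about 445 workers split 1:1 with no attrition; the 386 workers in Table 1, at the actual split, give about 0.33 and 0.30

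*Protocol article*

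**What the plan says.** The power paragraph in Results, after Table 2, covers three datasets. For workers, the effective sample sizes and intraclass correlations "were N_eff_ = 345 and 423, and ICC = 0.05 and 0.01, respectively" for physical and mental work ability. It continues: "The average cluster size in the workers sample was m = 6.53, which yields design effect estimates of DE = 1.29 and 1.05". From these it concludes that "it will be possible to estimate effect sizes of at least 0.30 and 0.27 at the 80% power and 5% significance levels". The Abstract ties the figures to the final analysis: "At the end of the trial, effect sizes of at least 0.30 and 0.27". The Discussion lists them as a strength, compares them with standardised effects of 1.23, 0.55 and 0.35 (absolute values) from earlier randomised organisational interventions, and concludes that "the present study has sufficient power to detect substantial changes in the main outcomes".

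Other parts of the article bear on the same figures:

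- The Abstract gives 174 workers in 22 intervention clusters and 276 in 47 control clusters, so 450 workers in 69 clusters.
- Table 1 describes 386 workers, with physical work ability missing for 4 and mental work ability for 6.
- Randomisation and implementation explains that the hospitals could not be allocated 1:1 and that cluster sizes vary widely. It justifies sampling proportional to size partly "to counter the expected power loss due to cluster and individual sample attrition in the subsequent follow-up measurements".
- Results reports that a "total of 67 clusters were defined", which differs from the Abstract's 69.

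**The concern.** The effective sample size of 423 for mental work ability is larger than the 386 workers in Table 1. Dividing 386 by a design effect above 1 cannot give 423, so the calculation must start from a larger number. The stated effects also look like the equal-arm formula, although the arms are unequal. The attrition that the article expects does not appear in a figure labelled as holding at the end of the trial.

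These figures concern the primary outcome, support the Discussion's claim about power, and will be used to interpret a null result. If the stated effects carry about 71% power rather than 80%, readers will be over-confident that an effect of that size has been ruled out.

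**Working it through.** **Reproducing the stated figures.** The article does not state sidedness; a two-sided 5% test reproduces its numbers. With z = 1.960 + 0.842 = 2.802 and intervention share p, the detectable standardised effect is d = 2.802 / sqrt(N_eff × p × (1 − p)). At p = 0.5 this is 2 × 2.802 / sqrt(N_eff):

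- Physical: 2 × 2.802 / sqrt(345) = 0.302.
- Mental: 2 × 2.802 / sqrt(423) = 0.272.

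The stated 0.30 and 0.27 therefore follow from the stated effective sample sizes, with equal arms.

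**Number of workers behind them.** Multiplying back by the design effect gives 345 × 1.29 = 445 and 423 × 1.05 = 444. The average cluster size agrees: 450 / 69 = 6.52, against the stated 6.53, whereas 386 / 69 = 5.59 and 386 / 67 = 5.76.

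**The other datasets in the same paragraph.** For patients, 632 / 2.7 = 234, the stated value, from the n in Table 2. For elderly care, 150 / 6.32 = 24, again as stated. Only the workers' figures start from more people than their table reports.

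**Actual split.** 174 / 450 = 0.387. With one age missing, the age percentages in Table 1 fit only 147 intervention to 238 control, or 0.382, so the 386 are unequally split as well.

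**Recalculation with 386 workers and the stated design effects** (p = 0.387, p(1 − p) = 0.237):

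| | Physical | Mental |
|---|---|---|
| N_eff = 386 / DE | 386 / 1.29 = 299 | 386 / 1.05 = 368 |
| d at 1:1 | 0.324 | 0.292 |
| d at the actual split | 0.333 | 0.300 |
| Power at the stated 0.30 / 0.27 | 71.5% | 71.3% |

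Most of the change comes from the number of workers; the split adds about 0.01. Using 147:238 gives 0.333 and 0.301. Recomputing the design effect at m = 5.59 gives 0.325 and 0.300.

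**Cluster-size variation.** The Sample size section gives the formula used: "a design effect DE = 1 + ICC*(m-1) = 1.33 was estimated" (cited here for its form only). It has no term for variation in size. With DE = 1 + ICC × ((1 + CV²) × m − 1), m = 6.53, the rounded ICCs and no attrition, an assumed CV of 0.5 to 1.0 gives 0.341 to 0.371 (physical) and 0.303 to 0.310 (mental). The text gives no CV.

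**Attrition.** The article gives no rate. Assume 10% to 30% loss, with m shrinking in step from 6.53 and no size variation. At 10% for physical: N = 347.4, m = 5.88, DE = 1 + 0.05 × 4.88 = 1.244, N_eff = 279, d = 0.344. At 30% for physical: N = 270.2, m = 4.57, DE = 1.179, N_eff = 229, d = 0.380. The mental range is 0.316 to 0.356.

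**The case against.** The strongest reply is that nothing has been miscalculated: given its effective sample sizes, the paragraph reaches the right effects. That is so, and the fault lies in the inputs. The flow diagram, which is not shown, may explain the fall from 450 to 386 and the two cluster counts. It cannot, however, make 386 workers yield an effective size of 423. Even with all 450 workers, the actual split gives 0.308 and 0.278.

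A second reply is that the final analysis may recover the loss. Statistical methods plans mixed models for longitudinal data, and imputation and sensitivity analyses for missing data. If baseline and follow-up correlate at r, adjustment scales the detectable effect by roughly sqrt(1 − r²); at an assumed r = 0.5, 0.333 becomes 0.29. This stands as a possibility, but the article gives no correlation and does not rest its figures on adjustment. It justifies quoting an adjusted figure separately, not leaving the unadjusted one as it is.

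A reader might also infer that the true detectable effect exceeds 0.35, so that the smallest cited effect is out of reach, or that the article calls 0.35 comfortably detectable. The document supports neither. On its own inputs both effects stay below 0.35. Crossing that value needs an attrition rate or a cluster-size CV that it does not give: with attrition alone, physical crosses at about 20% loss (0.360) and mental only near 30% (0.334 at 20%, 0.356 at 30%). The Discussion says only that earlier effects were larger than the trial's detectable effects.

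**Conclusion.** The stated detectable effects for the primary outcome are wrong as written. On documented inputs alone (386 workers, the actual split and the article's design effects) they are about 0.33 and 0.30 unadjusted, roughly 0.03 larger than stated. Power at 0.30 and 0.27 is about 71%. This rests on a two-sided test and the normal approximation, both of which reproduce the article's own figures.

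The end-of-trial label is unsupported because expected attrition is left out. How far the figures worsen by the final follow-up depends on assumptions: about 0.34 to 0.38 (physical) and 0.32 to 0.36 (mental) for 10% to 30% loss, before size variation and before any gain from baseline adjustment.

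The claim of sufficient power needs qualifying, not withdrawing. The margin against 0.35 is thin and may vanish with attrition; the cited effects of 0.55 and 1.23 stay detectable. The 67 versus 69 clusters are a minor, separate inconsistency that barely moves these figures.

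**What to change.** - In the Abstract, Results and Discussion, give the unadjusted detectable effects as about 0.33 and 0.30 on the 386 baseline respondents, and state the number of workers and the split used.
- Give a separate end-of-trial figure under an explicit attrition rate, with a design effect that includes the observed cluster-size CV. The investigators have the cluster sizes.
- If power is claimed for a baseline-adjusted analysis, quote that figure separately, with the assumed correlation.
- In the Discussion, say that the margin against the smallest cited effect is thin and may disappear with attrition, while the larger cited effects remain detectable.
- State why 450 workers become 386, and reconcile 67 with 69 clusters. The 10 + 10 hospital clusters plus 2 of the 4 elderly care wards give the Abstract's 22 intervention clusters.

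The cost is a recalculation and some rewording. Enrolment, allocation and the planned analysis are unaffected; the published figures become less favourable.

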## Methods

### Study design

The study is a two-arm, cluster-randomised intervention with healthcare workers conducted in seven general and three specialised hospitals, and an elderly care centre in Germany, whose wards constitute the clusters. A cluster-randomisation design was required due to the fact that it is an organisational workplace intervention whose main target are wards, and the randomisation of individuals is not feasible, since, in principle, the set of measures implemented in the intervention wards may affect all workers therein. A cluster-randomisation design helps reducing the risk of contamination effects between intervention and control wards and, at the same time, accounts for the correlations of individual measurements being observed within clusters. Outcome data are collected at baseline and at two follow-up times (T1 and T2) in surveys containing validated instruments. Data collection at baseline was performed before the interventions began in the intervention arm. The first follow-up measurement T1 in the single wards will be conducted successively no later than 6 weeks after the implementation of the first measures aiming to reduce the workload of healthcare workers. The final measurement T2 in all wards will be performed 12 months after the last T1 follow-up. Baseline data collection on workers and clients took place between June and December 2019. The follow-up measurements at T1 and T2 will take place in 2020 and 2021, respectively.

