#### Clients

The eligibility criteria for participation in the client surveys were being older than 18 years, being able to give informed consent to participation, being a responsive patient, and having sufficient skills in the German language. Clients (i.e. patients and individuals in elderly care in residencies and at home) are contacted in the participating healthcare organisations and receive a booklet with a brief description of the survey and data privacy information. All clients are required to consent explicitly to participate in the study before data collection. At baseline, T1 and T2 follow-up, approximately 600 patients and 150 individuals in elderly care will be surveyed successively in a cross-sectional design in the intervention and control wards. Participation in the client surveys is anonymous. The outcome data on clients are collected by interviewers either as self-administered questionnaires, or personal interviews upon clients’ request. The interviewers receive a three-hour training in survey methodology provided by the authors from Ulm University before data collection.

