## Conclusions

In conclusion, the results suggest that the implementation of the study design has been satisfactory so far. The intervention is expected to provide evidence of relatively small to medium-size effects of the intervention activities on the work ability of healthcare workers and on clients’ satisfaction with care.

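### The patient detectable effect of 0.21 comes from tripling a one-wave effective sample size, although the same wards are resurveyed and the baseline wave precedes the intervention

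*Protocol article*

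**What the plan says.** The power paragraph in Results (after Table 2) gives the patient inputs as "average ICC = 0.09, m = 19.5, and DE = 2.7", with an effective sample size of 234 for the baseline wave. It notes that "data of approximately 1200 additional patients will be collected cross-sectionally at the T1 and T2 follow-ups" and from this derives "a final effective sample size of approximately 234*3 = 702, and an average effect size of about 0.21", which "may be estimated at the 80% power and 5% significance levels".

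Two other places describe the design behind these figures. Participants, Clients: at each of the three time points, "approximately 600 patients and 150 individuals in elderly care will be surveyed successively in a cross-sectional design in the intervention and control wards". Study design: T2 is measured in all wards, and "Data collection at baseline was performed before the interventions began in the intervention arm".

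The elderly care figure in the same paragraph follows the same pattern: 24 per survey becomes a final effective size of 74 and a detectable effect of about 0.66.

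**The concern.** Tripling the effective size is valid only if each wave brings an independent set of wards and every wave informs the arm comparison equally. The design sections contradict both conditions.

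- New patients from wards already surveyed raise the cluster size m and leave the number of clusters unchanged. The design effect formula in Sample size, DE = 1 + ICC × (m − 1), must then use the accumulated m.
- Baseline patients were surveyed before any intervention. They can sharpen the comparison as a covariate, but they show no intervention effect.

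The figure of 0.21 is the only stated precision for patients. The Discussion says that the second hypothesis cannot be investigated with the elderly care data, so that hypothesis rests on the patient surveys. A null patient result read beside 0.21 would look more informative than the design allows.

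**Working it through.** **Inputs.** From Table 2: 632 baseline patients. From the power paragraph: ICC 0.09, m = 19.5, DE 2.7, and about 1200 further patients. Power is 80% and significance 5%. Sidedness is not stated; two-sided is assumed and reproduces the article's figure.

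**Formula.** Detectable effect = (1.960 + 0.842) / √(N_eff × p × (1 − p)), where p is the intervention share. At p = 0.5 this is 5.603 / √N_eff.

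**Reproducing the article.** DE = 1 + 0.09 × 18.5 = 2.665 (stated as 2.7). 632 / 2.7 = 234, and 234 × 3 = 702. 5.603 / √702 = 0.2115. This matches.

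**Number of wards.** 632 / 19.5 = 32.4. Three non-overlapping sets would need about 97 clusters. The article reports 67 in all (69 in the Abstract), four of them in elderly care. So the waves cannot be independent sets of clusters.

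**Same wards, article's own DE formula, equal arms:**

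| Patients counted | m | DE | N_eff | Detectable effect | Power at 0.21 |
|---|---|---|---|---|---|
| Three waves pooled (1896) | 58.5 | 6.175 | 307 | 0.32 | 45% |
| T1 + T2 (1264) | 39 | 4.42 | 286 | 0.33 | 43% |
| T1 + T2 (1200) | 37 | 4.24 | 283 | 0.33 | 42% |

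If T1 and T2 are generously treated as independent and only baseline is removed, N_eff = 468, the detectable effect is 0.26 and power at 0.21 is 62%. Removing baseline alone is therefore enough to lose 0.21.

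**Using baseline as a covariate.** Let ρ be the between-wave ward correlation. The article does not give it, so it is varied from 0 to 1.

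- Variance of a ward-wave mean: v = 0.09 + 0.91 / 19.5 = 0.1367.
- Variance of the T1/T2 average: (v + 0.09ρ) / 2.
- After adjustment for the ward's baseline mean: subtract (0.09ρ)² / v.
- N_eff = 32.4 / variance.

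At ρ = 1: 0.1133 − 0.0593 = 0.0541, so N_eff is about 600, the detectable effect 0.229 and power at 0.21 73%.

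| ρ | Adjusted, equal arms | Adjusted, 29:71 |
|---|---|---|
| 0 | 0.257 | 0.283 |
| 0.4 | 0.273 | 0.300 |
| 0.6 | 0.268 | 0.294 |
| 0.8 | 0.254 | 0.279 |
| 1 | 0.229 | 0.252 |

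A plain difference-in-differences gives 0.26 (ρ = 1) to 0.45 (ρ = 0) with equal arms.

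**Allocation.** The patient numbers by arm are not printed, but the Table 2 percentages determine them closely. Age is known for 628 patients. A split of 183 / 445 reproduces all six percentages: 32, 51 and 100 of 183, and 102, 171 and 172 of 445. The only other age solution found, 240 / 388, fails the sex percentages, whereas 184 / 446 fits them (92 of 184 and 210 of 446 male). So p is about 0.29, and each detectable effect is multiplied by 0.5 / √(0.292 × 0.708) = 1.10. The unadjusted T1 + T2 figure becomes 0.331 × 1.10 = 0.36. Even 702 itself would give 0.23.

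**Elderly care.** ICC 0.17 and m = 30.7 per survey. For two follow-up waves in the same wards, m = 61.4, DE = 1 + 0.17 × 60.4 = 11.27, N_eff = 300 / 11.27 = 26.6 and the detectable effect is about 1.09 with equal arms, against the stated 0.66. With four wards the normal approximation is itself doubtful, so this only indicates scale.

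**The case against.** The best case for the article is that the size of the shortfall is not fixed. It depends on the estimator and on the between-wave correlation, and neither is given. The most favourable baseline-adjusted case is 0.229, only about 9% above 0.21.

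The ICC may also overstate the variance that matters. Statistical methods fits clusters within organisations and randomisation was stratified by hospital, so part of 0.09 may be between-hospital variance that the model removes. If the within-hospital ICC were 0.03–0.05 (an assumption), the adjusted figure at ρ = 1 would be about 0.205–0.218 with equal arms and 0.226–0.240 at 29:71. Individual covariates could help a little more. This stands as a reason not to call 0.21 impossible. It does not rescue the calculation, which uses 0.09 and claims no such gain.

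A reader might also infer from Table 4 that precision is far worse. An SE of 0.09 set against outcome SDs of 0.44–0.55 suggests a one-wave detectable effect of 2.80 × 0.09 / SD = 0.46–0.57. The documents do not support this. The SE comes from Bayesian models that also contain four ward-level worker covariates. The residual variances of the same models (0.550–0.617, that is SDs of 0.74–0.79) exceed the raw SDs in Table 2, so the two tables are not demonstrably on one scale.

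Finally, 0.21 set no sample size and no decision rule, and satisfaction is the secondary outcome. That stands and lowers the severity.

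**Conclusion.** The point holds. 702 and 0.21 follow only if the three waves are independent sets of wards and baseline counts in full, and the article's own design description rules out both. At ICC 0.09 and the patient split implied by Table 2, the detectable effect is about 0.25–0.30 for the T1/T2 average adjusted for the ward's baseline mean (ρ from 0 to 1), and about 0.36 unadjusted with stable ward effects (ρ = 1). With equal arms the corresponding figures are 0.23–0.27 and 0.33.

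These rest on a two-sided 5% test, about 32 equally sized wards, follow-up waves about as large as baseline, and no further variance reduction. Unequal ward sizes and the modest number of wards would push the figures up.

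Two stronger readings are tempting. One is that 0.33 is the correct value; it is only the unadjusted case with equal arms and stable ward effects. The other is that the Conclusions are wrong to say that the trial is "expected to provide evidence of relatively small to medium-size effects". That sentence does not repeat 0.21, and effects of 0.25–0.36 still fit it, so it need not change. This should be fixed, but it concerns a secondary outcome and alters no design decision.

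**What to change.** Delete 234*3 = 702 and 0.21 from the power paragraph. State the patient detectable effect as a range, naming the estimator, the allocation, the ICC and the assumed between-wave ward correlation. At ICC 0.09 and about 29:71, this is about 0.25–0.30 for the T1/T2 average adjusted for the ward's baseline mean, and about 0.36 without adjustment. If a smaller within-hospital ICC is believed to apply, report its estimate and base the range on it.

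Recompute the elderly care figure (24 per survey, final 74, effect 0.66) in the same way, counting only post-intervention waves and using the accumulated cluster size.

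The cost is one reworded paragraph and less favourable stated precision. No further patients and no change to the analysis are needed.
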